### Pre-Participation Screening Measures

#### Foot and Ankle Ability Measure (FAAM)

The FAAM is a self-report questionnaire consisting of a 21-item ADL subscale and 8-item Sports subscale, in addition to a global rating of self-perceived foot function from 0-100% [41]. This inventory demonstrates satisfactory internal consistency, validity, and score stability. Test-retest validity is satisfactory for use in research designs involving repeated measures (ICC_2,1 _= .87-.89). Minimum clinically important change scores have been identified for the ADL subscale (8 points) and Sports subscale (9 points) with respect to patient global rating of change.

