#### Patient Global Rating of Change (GROC)

The GROC is a single item 15-point scale intended to measure a subject's general perception regarding response to treatment [54]. Responses range from "A very great deal better" to "A very great deal worse," with "About the same" serving as the center of the scale. GROC is a common scale used in studies that assess health-related quality of life due to its simplicity and face validity.

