### Data Analysis

The primary dependent variable for this study is FAAM score at 1 week, 4 weeks, 6 months, 1 year, and 2 years. Secondary dependent variables include NPRS, modified FABQ, PANAS, LExSES, and GROC scores at 1 week, 4 weeks, 6 months, 1 year, and 2 years. The independent variable is the manual therapy intervention condition. All other outcome measures will be assessed as potential covariates of treatment success, which is defined as the achievement of minimum clinically important change score on the FAAM for this study.

Descriptive statistics will be calculated for the data set, including frequencies, means, and standard deviations. Between and within-group comparisons will be made for outcome measurements at 4 weeks, 6 months, 1 year, and 2 years post-enrolment. Analysis of variance with appropriate post-hoc pairwise comparisons will be used to assess between-groups differences for continuous data. Statistical significance of between-group differences in categorical data will be assessed with chi square analysis. Pearson correlations and multivariate linear regression analyses will be performed to determine statistical significance of associations with treatment success and failure. An intention-to-treat analysis will be performed for subjects who drop out of the study after enrolment but prior to completion of all study procedures. Statistical significance of inferential statistical tests will be accepted at α≤.05.

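### Treatment success is a yes/no variable but is to be analysed with Pearson correlation and linear regression, under a covariate rule that, read literally, admits post-treatment scores including the global rating of change

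*Protocol article*

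**What the plan says.** All the relevant rules stand in the Data Analysis section of the protocol article.

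- Success is the attainment of a threshold: "which is defined as the achievement of minimum clinically important change score on the FAAM for this study".
- The candidate covariates are described in one clause: "All other outcome measures will be assessed as potential covariates of treatment success".
- The method is: "Pearson correlations and multivariate linear regression analyses will be performed to determine statistical significance of associations with treatment success and failure".
- Just before the covariate rule, the other outcomes are listed with their visits: "Secondary dependent variables include NPRS, modified FABQ, PANAS, LExSES, and GROC scores at 1 week, 4 weeks, 6 months, 1 year, and 2 years".

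Two measurement sections bear on this. The FAAM section gives two thresholds and their anchor: "for the ADL subscale (8 points) and Sports subscale (9 points) with respect to patient global rating of change". The GROC section describes that scale as "intended to measure a subject's general perception regarding response to treatment".

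For comparisons between arms, Data Analysis names analysis of variance for continuous data and chi-square for categorical data. No model for a binary response is named for the covariate analysis.

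**The concern.** A variable recording whether a threshold was reached takes two values. Pearson correlation and linear regression describe straight-line relations with a continuous response, so their estimates are hard to interpret here. The correlation depends on the success rate, and a linear model can return a fitted probability below 0 or above 1.

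The covariate rule raises a second problem. If other outcome measures means the scores listed at the follow-up visits, the analysis would relate FAAM success to pain, fear-avoidance, mood, self-efficacy and perceived change recorded after treatment, possibly at the same visit. Such scores share in the outcome and do not predict it. GROC is the clearest case: it asks how the patient responded to treatment, and the FAAM threshold was itself set against a global rating of change.

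Third, success is not fixed to a subscale or a visit. Two thresholds and five FAAM visits allow 2 × 5 = 10 definitions.

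At stake is any later statement about which patients benefit. It could rest on restatements of the outcome, or on chance findings among many tests.

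**Working it through.** The protocol gives no figure of its own for this analysis. What follows measures the three problems separately.

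**Inputs from the document.** 52 subjects per group before the dropout allowance (Subjects), so 3 × 52 = 156 completers; α = .05 for every test, with no adjustment stated (Data Analysis); the instruments in the baseline and post-treatment sections.

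**Assumptions, because the document is silent.** The success rate; the correlation between GROC and FAAM change; the number of candidates entered together.

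**1. Fit of method to outcome.** Pearson correlation with a yes/no variable is the point-biserial correlation. With 156 subjects and no true association, 3,000 simulated trials per setting rejected at these rates:

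| Success rate | Rejection rate at .05 |
|---|---|
| 50% | 0.050 |
| 70% | 0.046 |
| 90% | 0.049 |

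Test size is therefore about right. Estimation is less satisfactory. With one normal predictor and a true logistic relation, the share of linear fitted values outside 0 to 1 was 2.4% (intercept 0.4, slope 1 per SD), 6.9% (intercept 1.5, slope 1) and 11.7% (intercept 1.5, slope 1.5).

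**2. Covariates tied to the outcome.** Suppose GROC correlates r with FAAM change and success is the top share s of FAAM change, both normal. Then the correlation of GROC with success is r × φ(z) / √(s(1 − s)), where z is the normal cut-point. The factor is 0.3989 / 0.5 = 0.80 at s = 50% and 0.3178 / 0.4330 = 0.73 at s = 75%. The test statistic is t = c√(154 / (1 − c²)).

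| r (assumed) | c at s = 50% | t | c at s = 75% | t |
|---|---|---|---|---|
| 0.3 | 0.24 | 3.1 | 0.22 | 2.8 |
| 0.5 | 0.40 | 5.4 | 0.37 | 4.9 |
| 0.7 | 0.56 | 8.4 | 0.51 | 7.4 |

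Even a weak link makes GROC significant, whether or not it has any prognostic value. The table also shows that the same underlying r gives a different Pearson coefficient when only the success rate changes.

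**3. Number of tests.** Baseline candidates, counted from the measurement sections: NPRS 3, FABQ 2, LExSES 3, PANAS 2, range of motion 10, manual muscle tests 7, balance test 8 directions × 2 limbs = 16. The sum is 43. Adding the FAAM Sports subscale, the FAAM global rating and GROC gives 46.

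- Expected false positives if all are null: 43 × .05 = 2.15; 46 × .05 = 2.30. This does not need independence.
- Chance of at least one, if independent: 1 − .95^43 = 0.89; 1 − .95^46 = 0.91.
- Follow-up scores, if admitted: NPRS 3 + FABQ 2 + PANAS 2 + LExSES 3 + GROC 1 = 11 per visit. Over five visits that is 55, and 46 + 55 = 101 candidates, with 101 × .05 = 5.05 expected false positives.

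**4. Model size, only if everything is entered together.** If 20% to 50% of 156 subjects fall in the smaller outcome class, there are 31 to 78 limiting events. Over 46 candidates that is 31/46 = 0.7 to 78/46 = 1.7 events each. The expected R² with no true association is 46/155 = 0.30.

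**The case against.** The strongest reply is that post-treatment covariates are never stated. Data Analysis names the FAAM, then the secondary dependent variables, then the independent variable, and only then all other outcome measures. In that order the phrase could mean what has not yet been named: range of motion, muscle tests and the balance test, which appear only as baseline measures. Baseline questionnaire scores are another possible reading. On either of these there is no circularity. This stands as a limit. But the same paragraph lists NPRS, FABQ, PANAS, LExSES and GROC as outcomes at follow-up visits, so the literal wording admits them, and the rule should not leave it open.

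Second, the stated aim is statistical significance, and the tests keep their size. That is correct. A reader might infer that the significance tests are invalid; the simulation does not support this.

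Third, a reader might infer that adjusting for post-treatment scores would remove part of the treatment effect. The document does not support this either. Arms are compared by analysis of variance and chi-square with no covariates mentioned, and nothing says that the arm effect will be taken from the regression.

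Fourth, overfitting is not established. Candidates are to be assessed, not necessarily entered together, and an article may leave the selection step to a fuller document. The 89% to 91% figures assume independence, which 16 reach distances from one balance test do not have. The Background's favourable-outcome figure of about 75% comes from another sample under other treatment and cannot serve as this trial's success rate; hence the ranges above.

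Finally, the ADL subscale is probably intended, since eligibility and sample size both use it. The visit remains unstated.

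**Conclusion.** The point holds in a limited form. The mismatch between a yes/no outcome and the named methods is in the text and needs no assumption. The covariate rule is badly fixed: read literally it admits post-treatment scores, including GROC, and under an assumed correlation of 0.3 to 0.7 with FAAM change GROC would reach t of about 2.8 to 8.4 with 156 completers. Baseline measures alone give 43 to 46 candidates and about 2 expected false positives if all are null and each is tested once at .05.

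The harm is confined to the effect estimates, to covariates significant by construction if follow-up scores are used, and to unadjusted multiple testing. Per-test error rates stay near nominal and the randomised comparison is untouched. It should be corrected before the predictor analysis is run, but it does not threaten the trial's main result.

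**What to change.** Revise the Data Analysis section as follows.

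- Define success as a gain of at least 8 points on FAAM ADL, the scale and difference used for the sample size, at one stated visit. Four weeks is a natural choice: under Treatment schedule it is the last measurement before treatment choice is freed.
- Replace Pearson correlation and linear regression for this outcome with logistic regression containing arm, baseline FAAM ADL and a short pre-named list of baseline covariates. As a guide, if 10 limiting events per parameter are wanted (an assumption), 31 to 78 events carry about 3 to 7 parameters. Arm (two) and baseline FAAM ADL (one) take three of them.
- State that no post-randomisation measure, GROC included, is used as a predictor of success.
- Label any wider predictor search exploratory.

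Linear regression can remain for the continuous FAAM score. The cost is a change of wording, with no new data. The downside is fewer candidate predictors in the main model.

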## Discussion

This study protocol describes a randomized, placebo-controlled clinical trial that measures the short-, intermediate-, and long-term effects of talocrural joint mobilization, manipulation, and placebo treatment for individuals with post-acute ankle sprains. Hands-on treatments that improve ankle DF ROM are hypothesized to cause related improvement in disability and mitigation of re-injury risks. We believe the study designed in this paper addresses methodological deficiencies in the manual therapy literature to date that interfere with our optimal understanding of best practices related to mobilization/manipulation in individuals with post-acute ankle sprains. Specifically, inclusion of a hands-on placebo control should allow for differentiation of generalized clinical benefit from manual stimulation and clinician attention versus iatrogenic force application. In addition, the length of follow-up measurements should allow for adequate estimation of the potential longitudinal effects of mobilization/manipulation during the post-acute injury period on re-injury rate. The methodological characteristics of this study should help generate high quality data that will further our collective understanding of best practices in manual therapy.

## Abbreviations

ADL: activities of daily living; ATFL: anterior talofibular ligament; DF: dorsiflexion; FAAM: Foot and Ankle Ability Measure; FABQ: Fear Avoidance Beliefs Questionnaire; GROC: Global rating of change; ICC_2,1_: Intraclass correlation coefficient - formula 2,1; LExSES: Lower Extremity Self Efficacy Scale; MMT: manual muscle test; NPRS: numeric pain rating scale; PANAS: Positive and Negative Affect Scale; RCT: randomized clinical trial; RICE: rest, ice, compression, and elevation; ROM: range of motion
